### Randomization and blinding

Subject identification codes and corresponding treatment schedules, consisting of two treatment sequences randomized in small random block sizes, were developed by an independent biostatistician at the University of Calgary prior to initiation of the trial. Following informed consent, patients will be given the next available subject identification code and are then randomized to one of the two treatment sequences. The University of Calgary Research Pharmacy is the sole entity that holds the randomization list, and will prepare and dispense blister packs of the appropriate vitamin D supplementation for distribution to each subject accordingly upon email notification of recruitment. The study subjects, investigators, health care providers, study coordinators, and data analysts will be blinded to both the randomization schedule and subsequent treatment allocation.

On treatment days the hemodialysis nurses at each study site will administer the study drug to the subjects at the beginning of each dialysis session throughout the 24-week trial. Compliance with the vitamin D supplementation will be recorded on study drug administration schedules and checklists for each subject enrolled in the trial. To ensure blinding, all vitamin D combinations will be prepared in blister- packages by Research Pharmacy marked only with the participant’s study identification code. Each study capsule is packaged identically in1g soft gel capsules to ensure blinding. Specifically, each study capsule holds one 0.25mcg alfacalcidiol pill as well as a placebo or 50,000 IU ergocalciferol pill. Ergocalciferol has no distinct odour or taste. The Research Pharmacy has manufactured the VITAH placebo pills within each capsule to resemble the ergocalciferol pills in colour, shape, odour, taste and consistency to allow for a blinded controlled trial even if the study capsules are disassembled for the subjects to facilitate ingestion. To ensure compliance with the treatment, all blister-packs will be kept at the respective hemodialysis unit and study medications will be administered and recorded by the dialysis nurse (directly-observed therapy). Ergocalciferol (vitamin D_2_), in contrast to the other commercially available nutritional vitamin D, cholecalciferol (vitamin D_3_), is only available by prescription through a medical vendor and has been labeled with a federal Drug Identification Number through which product can effectively be tracked. This method allows the investigators to determine whether contamination is occurring during the study so it can be reduced and to determine its extent during the analysis phase. Subsequent statistical analyses will also be done blinded to the above treatment allocation.

### Data collection

Ambulatory electrocardiography (Holter) data is recorded for 18–24 hours using a standard bipolar 3-lead configuration (GE Healthcare, SEER MC; Milwaukee, USA). HRV is analyzed using a commercial Holter analysis system (MARS v. 7; GE Healthcare; Milwaukee, USA). Power spectral density analysis, which transforms the electrocardiographic signals into measures of frequency domain HRV (representing activity of the cardiac autonomic nervous system) are calculated. Autonomic activity is categorized into spectral bands: total power (TP), very-low frequency (VLF, 0.003-0.04 Hz), low-frequency (LF, 0.04-0.15 Hz) and high-frequency (HF, 0.15-0.4 Hz) domains [7,8,17-19]. Absolute LF and HF parameters are then squared and log-transformed (*ln* ms [2]) and converted to normalized units (nu). Overall cardiosympathovagal balance (LF:HF) is derived from these measures. Time domain HRV measurements are also calculated (Table 2) [7,8,17-19].

**Table 2 T2:** Description of heart rate variability data to be analyzed from 24- hour Holter recording

**Heart rate variability parameter (Acronym)**	**Description/Physiological representation**
**Low frequency (LF)**	Represents contribution of baroreflex activity in overall cardiovascular control
**High frequency (HF)**	Represents contribution of cardiac parasympathetic/vagal nervous activity
**Low to high frequency ratio (LF:HF)**	Represents the interplay between sympathetic and parasympathetic limbs of the autonomic nervous system
**Standard deviation of the normal**	
**Wave (SDNN)**	Variation (in units of standard deviation) between each successive R-wave in the ECG recording
**Standard deviation of the average**	
**Normal wave (SDANN)**	Average of the variation (in units of standard deviation) between each successive R-wave when comparing multiple 5-minute sections of the ECG recording
**Percentage of normal wave variation (pNN50%)**	Percentage of normal R-waves that differ from the wave directly before it by ≥50 milliseconds

The specific physiological parameters which will be assessed at each study visit throughout the study are described in Table 3. A MEDRIO electronic database (http://www.medrio.com) will be utilized for data entry after collection at baseline and every 6 weeks up to 24 weeks. Holter application and simultaneous blood draws will be collected at each study visit in order to observe potential vitamin D therapy-dependent changes in cardiac autonomic tone, circulating renin-angiotensin system activity markers, and mineral metabolism parameters related to vitamin D metabolism including serum calcium, phosphate, and parathyroid hormone. Blood samples collected from subjects at each study day are sent to the on-site laboratory typically used for other routine blood work at each of the study locations. Database access and ability to update blinded data will be provided only to the primary investigators.

**Table 3 T3:** Baseline and ongoing data collection

**Screening visit**	• Age, sex, target weight, duration on dialysis, cause of end-stage kidney disease, vascular access type
	• Serum calcium, phosphate, parathyroid hormone, Kt/V, 25-hydroxy vitamin D, 1,25-dihydroxy vitamin D
	• Medication use
	• GODIN leisure-time activity questionnaire
	• DASI aerobic capacity questionnaire
**Baseline study visit**	• Serum calcium, phosphate, parathyroid hormone, Kt/V, 25OHD level, 1,25-dihydroxy vitamin D level, catecholamines
	• Renin, aldosterone, angiotensin II
	• Delivered dose of dialysis (Kt/V)
	• Power spectral analysis (LF, HF, LF:HF) and time domain (SDNN, SDANN, pNN50%) HRV parameters
**Study visits every 6 weeks up to 24 weeks**	• Serum calcium, serum phosphate, parathyroid hormone, 25OHD, 1,25-dihydroxy-vitamin D, catecholamines
	• Renin, aldosterone, angiotensin II
	• Delivered dose of dialysis (Kt/V)
	• Power spectral analysis (LF, HF, LF:HF) and time domain (SDNN, SDANN, pNN50%) HRV parameters

### Primary outcome

The primary outcome of the study is sympathovagal balance (LF:HF), interpreted as the overall balance on stimulatory and inhibitory cardiac autonomic control, from baseline to the final study day within each 6 week treatment block (0 and 6 weeks, 18 and 24 weeks). Comparison of measured sympathovagal balance throughout each of the vitamin D supplementation treatment blocks as well as the 12-week washout period will allow for statistical interpretation of whether presence or absence of oral vitamin D therapy alters cardiac autonomic function within this population. An improvement in sympathovagal balance can be interpreted by a downward shift in LF:HF, in which a smaller value indicates greater contribution of cardioprotective vagal activity (Table 2).

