## Methods

### Study aims

The primary aim of the VITAH trial is to determine whether 6 weeks of intensive vitamin D supplementation, consisting of alfacalcidiol 0.25mcg orally at every dialysis session combined with ergocalciferol 50,000 IU orally once per week and placebo the remaining 2 weekly dialysis sessions, will influence HRV assessment of cardiac autonomic tone, compared to 6 weeks of conventional therapy with alfacalcidiol 0.25mcg and placebo orally at every dialysis session. The secondary aim is to determine whether this intensive vitamin D supplementation influences or modulates independent activity of the sympathetic and vagal limbs of the cardiac autonomic nervous system compared to the conventional alfacalcidiol regimen.

We hypothesize that vitamin D supplementation will increase *all* cardiac autonomic parameters, but that the vitamin D treatment will specifically have the greatest impact on vagal tone. We hypothesize that cardiosympathovagal balance will decrease after vitamin D therapy due to the fact that any increase in cardiosympathetic tone will be offset by a larger increase in cardiovagal tone.

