### Study design and setting

The VITAH Trial is a 2x2 cross-over, randomized-controlled trial with blinding of subjects, investigators, health care providers, as well as all study coordinators and data analysts. Hemodialysis outpatients from the Southern Alberta Renal Program will be randomized to one of two treatment sequence arms; 6 weeks of intensive vitamin D therapy (0.25 mcg alfacalcidiol at each dialysis session plus 50,000 IU of ergocalciferol once per week and placebo the remaining two weekly dialysis days), followed by a 12 week washout, and 6 weeks of conventional vitamin D therapy (0.25 mcg alfacalcidiol plus placebo at each dialysis session), or vice versa. Twenty-four hour Holter ECG monitors are applied within the first hour of the first weekly dialysis run at baseline and every 6 weeks throughout the entire 24-week duration of the trial (Figure 1). The study protocol will not impact on uremia clearance given that the dialysis prescription will remain constant. Subject recruitment began in January 2013 and will continue until 2016.

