### Study interventions

The intervention is the vitamin D therapy sequence, including 6 weeks of intensive therapy and 6 week of conventional vitamin D therapy, or vice versa (Figure 1). Given that the current clinical standard of care is use of activated vitamin D (one of the top drug classes prescribed as recently outlined in the United States Renal Data System [44]) in the ESKD population, a placebo arm is not included. Upon recruitment, participants who are prescribed any form of vitamin D (either nutritional or active) at that time will cease to take the medication for 4 weeks, a valid washout period employed by the PRIMO trial, a randomized controlled trial examining the effects of activated vitamin D on cardiac structure in subjects with non-dialysis dependent kidney disease [45]. Participants who are not on any form of vitamin D at the time of enrolment will be randomized to one of the two treatment sequences immediately. All participants will be randomized to Treatment Sequence 1 or Treatment Sequence 2, such that each participant will ingest both vitamin D therapy regimens in a randomized, blinded, placebo-controlled crossover design and thus act as his/her own control. A 12 week washout period was chosen between each 6 week vitamin D treatment block to ensure that there are no carryover effects from either study period as the t_1/2_ for alfacalcidiol is approximately 4 hours, and the t_1/2_ for ergocalciferol is 19–48 hours [22,23,46].

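### The Primary outcome section promises an answer on vitamin D versus no vitamin D, but randomisation supports only intensive versus conventional therapy

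*Protocol article*

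**What the plan says.** The Primary outcome section of the protocol article defines the outcome as LF:HF from the start to the end of each 6-week block (weeks 0 and 6, weeks 18 and 24). It then describes a wider comparison: "Comparison of measured sympathovagal balance throughout each of the vitamin D supplementation treatment blocks as well as the 12-week washout period". This is said to permit "statistical interpretation of whether presence or absence of oral vitamin D therapy alters cardiac autonomic function within this population". The sentence has no qualifier such as exploratory, descriptive or non-randomised.

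Other sections describe what is randomised:

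- Study interventions: because activated vitamin D is the current standard of care, "a placebo arm is not included". It adds that "each participant will ingest both vitamin D therapy regimens in a randomized, blinded, placebo-controlled crossover design". The placebo stands in for ergocalciferol only.
- Study design and setting: the comparator is "6 weeks of conventional vitamin D therapy (0.25 mcg alfacalcidiol plus placebo at each dialysis session), or vice versa", so it too contains an active vitamin D compound.
- Study interventions, on the gap between blocks: "A 12 week washout period was chosen between each 6 week vitamin D treatment block to ensure that there are no carryover effects". The washout has the same position in both sequences.
- Study aims: the intensive regimen is to be assessed "compared to 6 weeks of conventional therapy with alfacalcidiol 0.25mcg and placebo orally at every dialysis session".

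**The concern.** The sentence presents an effect of vitamin D against no vitamin D as something the trial will deliver, whereas the design randomises only the order of two vitamin D regimens. Whether a patient is on or off drug at a given visit is fixed by the calendar of the study and is identical in both sequences.

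Suppose LF:HF falls in both treatment blocks and the two regimens do not differ. The sentence would then offer prespecified support for concluding that vitamin D improves autonomic tone. That conclusion would rest on an uncontrolled within-patient comparison, and nothing in the text warns the reader of this.

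**Working it through.** **1. What the sample size is for.** Inputs from Sample size calculation: SD of the difference 4.53, α = 0.05, power 0.9 (printed as β), 20% reduction, 54 evaluable, 10% dropout. The base for the 20% is not stated. A base of 10, the cited quinapril baseline, is assumed here, so the difference is 2.0.

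n = (4.53 × (1.960 + 1.282) / 2.0)² = 53.9, rounded up to 54; 54 / 0.90 = 60.

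Both printed figures reproduce (two-sided test). With a base of 9.5 the formula gives 60, and with 9 it gives 67. The calculation is stated for combined vitamin D against alfacalcidiol alone. No number in the section is for treated against untreated.

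**2. On/off status by visit.** Holters are recorded at baseline and every 6 weeks to week 24 (Study design and setting). In both sequences:

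| Week | 0 | 6 | 12 | 18 | 24 |
|---|---|---|---|---|---|
| Status | off | on | off | off | on |

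No visit has one sequence on drug and the other off, so a comparison between randomised groups carries no information on drug against no drug. What remains is within-patient change.

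**3. What within-patient change can and cannot separate.** Let d be a linear drift per 6 weeks and T the drug effect at weeks 6 and 24, averaged over the two regimens.

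- *Change within a treated block* (0 to 6, or 18 to 24): T + d. The full drift is included.
- *Mean of on-drug visits minus mean of off-drug visits*: the average weeks are (6 + 24)/2 = 15 and (0 + 12 + 18)/3 = 10. The 5-week gap leaves (5/6)d.
- *Mean of the two block changes minus half the week 6 to 18 change*, with Y the LF:HF value at each week: −½Y0 + Y6 − Y18 + ½Y24.
  - Linear drift: d − ½(2d) = 0, so it is removed.
  - Drug effect: T + ½T = 1.5T, so it is kept.
  - Quadratic trend (0, q, 9q, 16q at weeks 0, 6, 18, 24): q − 9q + 8q = 0, so it is also removed.
  - Entry effect, where week 0 alone is higher by e: −½e remains. Divided by 1.5, it reads as a drug effect of −e/3.
  - Residual drug effect, a fraction r of T still present at week 18: T − rT + ½T = (1.5 − r)T, so the drug effect is understated.

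The third contrast handles steady drift and simple curvature. It does not handle a shift confined to the start of the study. Two such shifts are plausible: regression to the mean after entry, and recovery from stopping earlier vitamin D. The second applies only to patients who were taking vitamin D, since Study interventions sends the others straight to randomisation.

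**The case against.** Untreated observations do exist. The sentence rests on the washout, and the off-on-off-off-on pattern is informative. A reader might infer that on/off status is wholly tied to study time and that no drift can be told from a drug effect. The algebra above shows otherwise: a linear drift cancels, and the two off-drug visits at weeks 12 and 18 show drift directly. Time on dialysis only increases, so it does not follow an on-off-on pattern. Entry-related effects act mainly on weeks 0 to 6 and would not naturally recur in weeks 18 to 24. Recruitment from 2013 to 2016 spreads season across study weeks. On the half-lives quoted in Study interventions, little drug should remain by week 12: 6 weeks is 1,008 hours, or 21 half-lives at the longest quoted value of 48 hours. Those half-lives describe the drug, however, and not how long any effect on heart rate variability lasts.

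A reader might also infer a specific false-positive rate. With 54 patients and an assumed drift of 0.5 to 1.0 units per block, a before-after test would reject with probability 0.20 to 0.62 in one block (SD 4.53/√2 = 3.20), or 0.36 to 0.89 for the mean of two (SD 4.53/2 = 2.27). With SD 4.53 the figures are 0.13 and 0.36. The document gives no drift, these SDs are assumptions, and such tests ignore the washout visits. The figures illustrate the mechanism and do not measure the error.

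Finally, the aim, the primary analysis and the sample size all concern the two regimens, no on/off hypothesis test is named, and an analysis plan that is not shown may label the contrast exploratory. This limits the consequence. It does not remove the point, which concerns a positive statement in the article and not an omitted detail.

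What stands against all of this is that adjustment for time works here only through an assumed shape for the time course. Randomisation contributes nothing to it.

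**Conclusion.** The point holds in a limited form. The sentence claims more than the design supports. Randomisation supports intensive against conventional therapy, that is, ergocalciferol added to alfacalcidiol. It gives no information on vitamin D against no vitamin D, because none of the approximately 60 planned patients is allocated to be untreated and the on/off schedule is the same in both sequences.

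The on-treatment versus washout comparison has descriptive value, and linear drift can be removed from it. It stays open to entry effects, to other non-linear time effects outside the assumed shape, and to residual drug effect, which on the algebra above would understate a drug effect and not create one. A simple before-after change within blocks is weaker still, since it carries all of the drift.

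No numerical size can be given without assuming a drift. A reader might conclude that the trial's main result is compromised, but the documents do not support that: the randomised comparison and its sample size do not depend on this sentence. The visit schedule used here rests on the stated 6-week Holter interval and a washout in the same place for everyone.

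**What to change.** Reword the sentence in Primary outcome along these lines: *The confirmatory inference is the comparison of intensive with conventional vitamin D therapy. Any comparison of on-treatment with washout visits is exploratory and non-randomised, uses the washout visits to account for time trend, and will not be reported as evidence of an effect of vitamin D against no vitamin D.*

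A ban on any test of the on/off contrast is not needed, provided it is labelled in this way and is not a plain before-after test within blocks.

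The change is to wording only. It needs no extra patients or visits and leaves the regimens as they are. The cost is that a non-randomised claim is given up.

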### Secondary outcomes

The secondary outcomes include additional measures of cardiac autonomic tone, including LF, HF, as well as time domain parameters of HRV including the standard deviation of the normal R-R interval (SDNN), standard deviation of the average normal R-R interval (SDANN), percentage of normal R waves occurring ≥ 50 ms after the R waves immediately before (pNN50%), as well as blood draw measurements related to vitamin D metabolism at the beginning and termination of each 6 week treatment block (Table 2).

### Subject follow-up procedures

Subjects will be followed from trial entry until study completion (24 weeks study period). The study coordinator will review each subjects’ collected data at 6 week intervals to record primary and secondary endpoints, as well as to assess the safety and efficacy of the vitamin D administration in relation to study blood work. Study medication may be discontinued for reasons associated with concern for subject safety, or as requested by the subject or primary nephrologist.

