Evidence to date supports the safety profile of vitamin D therapy. Vitamin D deficiency is the norm in hemodialysis patients and as such, vitamin D supplementation should result in significant increase vitamin D levels. Secondly, given there is significant controversy regarding the target 25-hydroxyvitamin D level in both the general and chronic kidney disease population [38,39], we aimed to determine the effect of delivered dose of vitamin D, rather than level of vitamin D, on cardiac autonomic tone. Lastly, though there is significant practice variation, the activated and nutritional vitamin D doses chosen for the study reflect those recommended in and typically prescribed to the end-stage kidney disease population on hemodialysis [38].

Despite the high prevalence of vitamin D deficiency in ESKD, current guidelines regarding correction of vitamin D status are widely acknowledged to be opinion-based and derived from biochemical endpoints [38]. The nutritional vitamin D product (ergocalciferol) and dose proposed within this protocol is identical to that suggested by guidelines for treatment in the ESKD population [38,40]. Furthermore, treatment with other nutritional forms of vitamin D_3_ at a dose of 15,000 IU/day × 1 month [41] and 40,000 IU/day over 28 weeks, followed by 10,000 IU/day × 12 weeks [42] has been shown to be safe. A main clinical concern with activated vitamin D supplementation in the ESKD population is hypercalcemia, hyperphosphatemia and reduction in parathyroid hormone levels. This protocol employs the lowest possible dose of activated vitamin D (alfacalcidiol) available to minimize significant fluctuations in these biochemical values, though the relative importance of these changes remains unquantified within the literature [43].

In summary, the evidence to guide treatment that may minimize SCD and cardiovascular risk in ESKD is extremely limited. The VITamin D supplementation and cardiac Autonomic tone in Hemodialysis (VITAH) study is the first clinical trial to assess whether various vitamin D therapies, specifically ingestion of the combination of activated and nutritional vitamin D compared to activated vitamin D alone, influence cardiac autonomic tone and therefore cardiovascular risk in ESKD patients requiring hemodialysis.

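### The coordinator is declared blinded, yet the 6-weekly review covers 25OHD, the laboratory value most likely to suggest which regimen a subject received

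*Protocol article*

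**What the plan says.** - **Who is blinded.** Randomization and blinding states: "The study subjects, investigators, health care providers, study coordinators, and data analysts will be blinded to both the randomization schedule and subsequent treatment allocation". Study design and setting says the same.
- **Who looks at the data.** Subject follow-up procedures states: "The study coordinator will review each subjects’ collected data at 6 week intervals to record primary and secondary endpoints". The sentence goes on to say that the coordinator should "assess the safety and efficacy of the vitamin D administration in relation to study blood work".
- **What the blood work contains.** The first line of Table 3 for the visits every 6 weeks reads: "Serum calcium, serum phosphate, parathyroid hormone, 25OHD, 1,25-dihydroxy-vitamin D, catecholamines".
- **What counts as a secondary endpoint.** Secondary outcomes includes "blood draw measurements related to vitamin D metabolism at the beginning and termination of each 6 week treatment block".
- **Where samples go.** Under Data collection, blood samples "are sent to the on-site laboratory typically used for other routine blood work at each of the study locations". The same section limits database access, and the ability to update what it calls blinded data, to the primary investigators.
- **What is expected of the levels.** The vitamin D part of the Background says that, because deficiency is the norm in these patients, "vitamin D supplementation should result in significant increase vitamin D levels".

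**The concern.** The product is masked with care: matched capsules, pharmacy-prepared blister packs and a randomization list held only by the research pharmacy. None of this covers the laboratory results. A role that must stay blinded is assigned to review, and to judge efficacy from, results that include the analyte most directly fed by the one ingredient that differs between regimens.

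A crossover makes this worse than a parallel design would. With two sequences, a good guess about block 1 is also a guess about block 2, made before block 2 starts. If those around the subject hold such a guess, decisions about discontinuing study drug or withdrawing a subject may no longer be independent of allocation. At stake is the credibility of the blinding claim and, through withdrawals, possibly the primary comparison.

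**Working it through.** The article gives no figure for the strength of the blind or for the 25OHD response, so there is none to reproduce. The sample size does not enter this point.

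**1. Does the stated procedure put 25OHD before a blinded role?**
- The coordinator is blinded (Study design and setting; Randomization and blinding).
- The coordinator reviews collected data every 6 weeks and records secondary endpoints (Subject follow-up procedures).
- Secondary endpoints include vitamin D blood measures at the start and end of each block (Secondary outcomes).
- 25OHD is measured at every 6-week visit (Table 3).

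Followed as written, these steps take 25OHD to the coordinator. The article mentions no masking of it.

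**2. Does 25OHD separate the regimens?**
- Each capsule holds alfacalcidiol 0.25 mcg in both regimens; the second pill is ergocalciferol 50,000 IU or placebo (Randomization and blinding).
- Ergocalciferol over a block: 6 weeks × 50,000 IU = 300,000 IU in the intensive regimen, against 0 in the conventional one.
- The liver step from nutritional vitamin D to 25OHD is described as largely substrate driven (Background, Vitamin D).

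A difference in 25OHD change is therefore expected. Its size is not given.

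**3. How strong might the signal be?** *Assumption:* the 25OHD change is normal with equal SD under both regimens, the two regimens are equally likely in block 1, and the reader classifies at the midpoint. With *d* the difference in mean change divided by the SD, the probability of a correct guess from one result is Φ(d/2).

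| Assumed d | Φ(d/2) |
|---|---|
| 0.5 | 60% |
| 1 | 69% |
| 1.5 | 77% |
| 2 | 84% |
| 3 | 93% |
| 4 | 98% |

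Chance is 50%. The documents do not say where in this range the trial would fall.

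**4. When does the exposure matter?**
- Time after week 6: 24 − 6 = 18 weeks. Of these, 12 are washout without study drug, leaving 18 − 12 = 6 weeks of treatment, namely block 2.
- Holter application and blood draw are simultaneous, so block-1 dosing is complete and the week-6 recording has begun before a week-6 result exists.

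**5. Is there a route to the primary outcome?** Study drug may be stopped over a safety concern, or at the request of the subject or primary nephrologist (Subject follow-up procedures). Withdrawal can also follow a request, and withdrawn subjects are handled by last observation carried forward (Study withdrawal). If a subject is withdrawn after week 6 and before the week-24 recording, the last LF:HF value fills week 24, and week 18 too if that is missing. Block-2 change = LF:HF(24) − LF:HF(18) = 0. A withdrawal influenced by a guess at allocation would thus enter the primary comparison as a zero change.

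**The case against.** The best counter-argument is that a journal article condenses the full protocol, and that routing of laboratory results often sits in a laboratory manual. Mere silence about masking would be no finding. But the article is not merely silent: it gives a blinded role a task that, taken with Table 3 and the secondary outcomes, includes this analyte and asks for a judgement of efficacy. That conflict stands.

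Several stronger readings are tempting, and the documents do not support them:

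- **That the week-6 result reveals every subject's sequence.** No response size or SD is given. The expected rise is stated for vitamin D supplementation generally, and both regimens are vitamin D therapy. The article also names sources of noise: seasonal sunlight and possible contamination. At the low end of the assumed range, guessing is little better than chance.
- **That investigators review these results.** Only the coordinator is named. Investigators come in through database access, and what blinded data means there is unclear; it might or might not exclude 25OHD.
- **That the blind is lost for 18 of 24 weeks.** Twelve of those weeks are washout.
- **That 1,25-dihydroxyvitamin D is a second disclosure route.** Both regimens contain the same alfacalcidiol dose, and the article describes reduced renal 1α-hydroxylase in these patients. Nothing shows that this analyte separates the arms.
- **That unblinded staff would edit Holter recordings or change co-treatment.** No passage assigns the coordinator either task. HRV comes from a commercial analysis system and dosing is directly observed, which limits the room for bias.

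**Conclusion.** The point holds in a limited form. The coordinator's blinding and the coordinator's 6-weekly review of blood work conflict as written, because that review includes 25OHD. Unmasking is probable for an individual subject, not certain. It rests on the inference that ergocalciferol raises 25OHD more than placebo does, which the article's own account of vitamin D metabolism supports without giving a size.

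The exposure is mainly the 6 weeks of block 2, plus decisions on discontinuation or withdrawal after week 6. Primary investigators may also be exposed, depending on what blinded data means. Bias in LF:HF cannot be quantified from the documents and may be modest. No sample-size figure changes. This should be corrected, but it does not by itself invalidate the design.

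**What to change.** - State that post-baseline 25OHD results are withheld from coordinators, investigators and treating staff until database lock, for example by batching the assays or routing results to the unblinded pharmacy or the Data Safety Monitoring Board.
- Remove efficacy from the coordinator's 6-weekly blood-work review, so that it covers safety only.
- Say what blinded data means for the database, and that it excludes post-baseline 25OHD until lock.
- Withholding 1,25-dihydroxyvitamin D as well is an optional precaution.

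The cost is a laboratory instruction and a few sentences in the protocol. The downside is small: the care team does not see 25OHD during the trial. The Background says the trial tests delivered dose rather than level, and the article describes no titration on 25OHD. The calcium, phosphate and parathyroid hormone results, which relate to the main concerns it names for activated vitamin D, are untouched by this change.
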